### Outcomes

#### Primary outcomes

There are two primary outcomes in this trial. The primary outcome of pain will be changes in Numerical Rating Scale (NRS) and the primary outcome of function will be changes in the Knee injury and Osteoarthritis Outcome Score (KOOS) Activities of Daily Living (ADL) [29] from baseline at week 8. NRS is an 11-point pain assessment scale ranging from ‘no pain’ (0) to ‘worst pain’ (10). KOOS is an extension of the Western Ontario and McMaster University Osteoarthritis Index (WOMAC) [30], designed to evaluate knee injuries and osteoarthritis. KOOS Activities of Daily Living (ADL) subscale comprises 17 items and has a score range of 0–100, with lower scores indicating worse dysfunction.

#### Secondary outcomes

The secondary outcomes of this study include self-reported outcomes, objective outcomes of physical function, and a biological indicator outcome.

KOOS Pain [29]: A 9-item pain evaluation scale, with scores ranging from 0 to 100. Lower scores indicating greater levels of pain.

KOOS knee-related Quality of Life (QOL) [29]: A 4-item quality of life evaluation scale, with scores ranging from 0 to 100. Lower scores indicating poorer quality of life.

Short Form 6 Dimensions (SF-6D) [31]: A quality of life evaluation scale derived from the SF-36, with 6 items for estimating the cost-effectiveness. Higher scores indicating poorer quality of life.

Five-level EuroQol five-dimensional questionnaire (EQ-5D-5L) [32]: A generic preference-based quality of life evaluation scale, with 5 items for jointly estimating the cost-effectiveness. Higher score indicates poorer quality of life.

Credibility/Expectancy Questionnaire [33]: A 6-item scale for evaluating patients’ credibility/expectancy to the intervention. This scale will be measured within 5 min after the finish of first treatment.

Patient’s global assessment (PGA) [34]: A 5-point ordinal scale for evaluating the patient’s overall perception of the effect.

Thirty-second Chair Stand Test (30s-CST) [35]: A test of lower body strength, dynamic balance and sit-to-stand activity. The patient will be requested to sit in a chair with their feet flat on the floor, shoulder width apart, knees bent slightly more than 90 degrees, arms crossed at wrists and close to their chest. Then, within 30 seconds, the patient will be measured the times they could complete as many full stand-to-sit cycles as possible. The hips and knees require be fully extended when standing up; the hips require to fully touching the chair when sitting down. Additionally, the height of chairs needs to be unified.

Forty meters (4x10m) Fast Paced Walk Test (40m FPWT) [36]: A test of walking speed over short distances and changing direction during walking. Patients will be asked to walk back and forth twice on the 10-meter walkway completely as fast as possible without running. The time spent walking on the walkway will be recorded.

Daily Physical Activity level (DPA): DPA contains 1 week’s daily average steps and walking time, which will be recorded by portable pedometers (Polygon H-215G; Bestek Electronics Co., Ltd, Taiwan, China). The patient will be provided with a pedometer at the commencement of the preparatory period. The pedometer is required to be worn at all times except sleeping, bathing and water sports. At each visit, the researcher will record the data collected by the pedometer for the preceding week.

Rescue medicine: Any use of rescue medicine will be recorded, including the time and dosage.

The Credibility/Expectancy Questionnaire will be measured within a 5-minute period following the initial treatment session. PGA will be measured at week 4, 8, 16 and 24. Rescue medicine will be recorded within 24 hours after each taking. Other secondary outcomes will be assessed at baseline and at week 4, 8, 16 and 24. Additionally, the NRS and the KOOS ADL will be assessed at week 4, 16 and 24 as secondary outcomes.

### Adverse events

The safety of both treatments will be assessed by adverse events. Researchers and experts will determine whether any adverse events are related to the intervention within 24 hours of their occurrence. Serious adverse events will be referred to the principal investigator for further judgment and treatment. Common adverse events associated with electroacupuncture include pain, local haematoma, infection and dizziness. Common adverse events associated with exercise therapy include pain, muscle strain, spasm and joint swelling.

### Data management

All data will be recorded in detail on the case report forms, and any additional information or modifications need to be signed by the researcher. The completed CRF will be in the custody of two independent researchers who will input data doubly for proofreading. Any raw data will be stored for a period of five years post-study completion to enable readers to access these data by contacting the corresponding author, with the exception of patient-identifiable information.

### Sample size

Based on previous study [13,37], we estimated that the difference in effect size between the 2 groups would be no more than 0.5. Between-group variations in NRS and KOA were expected to be 1 and 8 at week 8, respectively, with the standard deviations (SD) of 2 and 16. With 2-side α = 0.025 (adjusted for two primary outcomes), 77 patients per treatment group are required to test a difference in effect size of 0.5 with 80% power. Taking into account a 20% dropout rate, a total of 196 patients are expected to be recruited.

### Statistical analysis

SPSS 26.0 software will be used for statistical processing. Measurement data will be expressed as mean and standard deviation, or median and interquartile ranges. Counting data will be expressed as percentages.

All randomly grouped patients with at least 1 session of intervention received will be included in the modified intention-to-treat (mITT) analysis. Multiple imputation will be used to fill the missing data. Five datasets for the missing data will be imputed by the observation value of age, gender, body mass index, KL grade and outcomes from other timepoints. All between-group comparison on repeated measure continuous outcomes (NRS, KOOS ADL, KOOS QOL, SF-6D, EQ-5D-5L, 30s-CST and 40m FPWT, DPA, except PGA) will be assessed by mixed-effect models using outcome scores at all assessed timepoints as the dependent variable, intervention as the main factor, and the baseline value as the covariate. PGA will be assessed by chi-squared test. Sensitivity analysis will be conducted on the primary outcomes (NRS and KOOS ADL) in 2 datasets. First, the dataset without imputation will be analyzed to address potential imputation bias. Second, the per-protocol (PP) set, which will be defined as receiving a minimum of 19 (electroacupuncture) or 12 (exercise) sessions with no obvious protocol violation, will be analyzed to address the compliance. For primary outcomes, *P* < 0.025 will be considered statistically significant (Bonferroni correction). Secondary outcomes will be considered exploratory, and *P* < 0.05 will be considered statistically significant.

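### Five imputed datasets are few for a primary test at P < 0.025 with 20% dropout allowed for; at least 50 would remove avoidable seed noise from borderline results

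*Protocol article*

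**What the plan says.** In the protocol article, the Statistical analysis section defines a modified intention-to-treat set of randomised patients who received at least one session, and for it states "Multiple imputation will be used to fill the missing data". It then prints the number: "Five datasets for the missing data will be imputed". The predictors are age, gender, body mass index, KL grade and outcomes from other visits. Each of the two primary outcomes (change in NRS and in KOOS ADL at week 8) is significant if P is below 0.025, by Bonferroni correction.

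Two further analyses of the primary outcomes are labelled as sensitivity analyses: one on the data without imputation and one on the per-protocol set.

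The Sample size section gives the expected loss: "Taking into account a 20% dropout rate, a total of 196 patients are expected to be recruited". The Health economic evaluation section computes QALYs from the multiply imputed data.

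**The concern.** Multiple imputation adds random noise of its own. Two analysts with the same data, the same model and different seeds get slightly different pooled estimates, standard errors and P values. The noise shrinks as the number of imputed datasets, m, grows. With m = 5 and an appreciable share of missing information, it may be large enough to move a P value near 0.025 across the threshold.

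What is at stake is the verdict on a primary outcome when the evidence is borderline. In that situation the declared result would depend partly on an arbitrary draw that a larger m would almost remove. The article prints the number five, so this is a stated choice and not a detail left to a separate analysis plan.

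**Working it through.** **Inputs from the protocol article.** m = 5 and threshold P < 0.025 (Statistical analysis); two-sided α = 0.025, 80% power, effect size 0.5, 77 per group, 20% dropout, 196 in total (Sample size).

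**Input not in the documents.** The FMI. It depends on how much dropout occurs by week 8 and on how well other visits predict the missing value. Simulated trials with 98 per arm, between-visit correlation 0.3 to 0.7, and 10% or 20% missing at week 8 gave an FMI of about 0.09 to 0.21. The range 0.1 to 0.2 is therefore assumed.

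**1. The plan's own figure.** The critical value is z(0.9875) = 2.241, and z(0.80) = 0.842. Then n = 2 × (2.241 + 0.842)² / 0.5² = 76.04, so 77 per group, as stated: "77 patients per treatment group are required to test a difference in effect size of 0.5 with 80% power". With the t distribution it is 78. Dividing by 0.8 gives 97 or 98 per group, so 194 to 196 in total. The sample size reproduces.

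**2. Seed noise.** The between-seed SD of the pooled estimate, in units of its standard error, is about √(FMI/m).

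| FMI | m = 5 | m = 50 |
|---|---|---|
| 0.1 | √0.02 = 0.141 | √0.002 = 0.045 |
| 0.2 | √0.04 = 0.200 | √0.004 = 0.063 |

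**3. Effect on a P value at the threshold.** For a result whose P with unlimited imputations is 0.025, the central 95% range over seeds is z = 2.241 ± 1.96 × SD, converted to a two-sided P.

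| FMI | m = 5 | m = 50 |
|---|---|---|
| 0.1 | 0.012 to 0.050 | 0.020 to 0.031 |
| 0.2 | 0.0085 to 0.064 | 0.018 to 0.034 |

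The simulation, which used a week-8 ANCOVA with Rubin's rules, also includes the instability of the between-imputation variance. At m = 5 it gave wider ranges: 0.011 to 0.064 with 10% missing at week 8, and 0.007 to 0.10 with 20% missing.

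**4. Where it can change a verdict.** At m = 5 and FMI 0.2:
- an exact P of 0.005 ranges over 0.001 to 0.016 (stays significant);
- an exact P of 0.01 ranges over 0.003 to 0.029 (can cross);
- an exact P of 0.05 ranges over 0.019 to 0.117 (can cross);
- an exact P of 0.1 ranges over 0.042 to 0.210 (stays non-significant).

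At FMI 0.1 the window is narrower: an exact P of 0.01 reaches only 0.022, and one of 0.05 falls only to 0.0253.

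**5. How often this happens.** Under the design alternative, z is taken as normal with mean 0.5 × √(77/2) = 3.10 and SD 1. Adding independent seed noise with the SDs of step 2 and integrating over z gives the probability that the reported verdict differs from the unlimited-imputation verdict, per outcome:

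| FMI | Alternative, m = 5 | Alternative, m = 50 | Null, m = 5 | Null, m = 50 |
|---|---|---|---|---|
| 0.1 | 3.1% | 1.0% | 0.8% | 0.2% |
| 0.2 | 4.4% | 1.4% | 1.1% | 0.3% |

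The simulation asked a different question: how often do two seeds at m = 5 disagree with each other under the design alternative? It gave about 4 to 11% of trials with 20% missing at week 8 and about 1 to 4% with 10% missing. With only 60 simulated trials per scenario this is a rough check, but the order of size agrees.

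**The case against.** The strongest case against is about weight, and most of it stands.

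- **An FMI of 0.2 is near the top of the plausible range.** The 20% is a sample-size allowance over a 24-week trial, and the primary time point is week 8, so some losses may come later. Patients with no session leave the analysis set and are not imputed. Outcomes at other visits recover some information. This is why 0.1 is shown alongside 0.2.
- **Borderline figures do not describe trials in general.** In simulated datasets selected to have an exact P of 0.015 to 0.04, the verdict flipped in about 39% of m = 5 reruns and still in about 19% at m = 50. A reader might infer that the primary conclusion is broadly irreproducible. Under the normal model of step 5, only about 10% of trials fall in that window under the design alternative and 2.5% under the null, so the unconditional rates apply.
- **Five imputations are imprecise, not invalid.** Rubin's rules allow for finite m. At FMI 0.2 the standard error grows by about 2%, since √(1 + 0.2/5) = 1.02. No bias follows.
- **A seed-free analysis is planned.** The data without imputation will be analysed for both primary outcomes, so a verdict created by imputation noise could show up as a discrepancy. This is a partial answer: it is a sensitivity analysis and does not set the primary verdict.
- **The simulated model is not the planned one.** The plan uses a mixed model over all visits, whose FMI was not computed and may differ somewhat.

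A reader might also carry the argument over to the cost-effectiveness result. The QALYs do use the imputed data, but the article plans an ICER with no significance threshold, so the verdict-flipping argument does not transfer and no size can be given.

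**Conclusion.** The point holds as a cheap improvement in precision and reproducibility, not as a flaw that undermines the trial. With m = 5, the P value of a primary result at the threshold varies about four- to eightfold across the central 95% of seeds (0.050/0.012 ≈ 4; 0.064/0.0085 ≈ 8). With m = 50 it varies less than twofold (0.031/0.020 ≈ 1.6; 0.034/0.018 ≈ 1.9). The declared verdict is at risk only for an exact P of roughly 0.01 to 0.05; clear results are unaffected. Going from 5 to 50 imputations removes about two-thirds of the avoidable discordance under the design alternative: from 3.1% to 1.0% at FMI 0.1, and from 4.4% to 1.4% at FMI 0.2.

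This rests on an assumed FMI of 0.1 to 0.2, a normal approximation for the pooled test statistic, and the trial's own effect size and evaluable sample. The documents do not support saying that the primary conclusion generally depends on the seed, or that the estimate is biased.

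**What to change.** In the Statistical analysis section, replace the five imputed datasets with at least 50, and state that the QALYs use the same imputed datasets. Fixing the seed in advance and reporting the Monte Carlo error of the primary estimates are sensible but optional, and can go in the analysis plan. A fixed seed alone would make the number repeatable while leaving it an arbitrary draw, so it does not replace the larger m.

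The cost is one number in the text and a few minutes of computing. Sample size, data collection and design do not change. The Study status section describes recruitment as under way, so the change can be recorded before the data are analysed.

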### Health economic evaluation

An economic evaluation will be conducted from a societal perspective. At the conclusion of the 8-week treatment period, the costs associated with electroacupuncture or exercise therapy will be summarized. Since participants will not be permitted to undergo any other treatments during the study period, only study-related direct medical costs and direct non-medical costs will be calculated. These include registration fees, treatment fees, transportation costs, and any associated delays. Direct medical costs will encompass registration and treatment fees. The registration fee for each treatment will be estimated based on the patient’s self-reported choice of registered doctor. Treatment fees will be determined according to the real-time treatment prices provided by the National Medical Security Bureau. Non-medical costs will be derived from patient-reported values. QALYs for each patient over the study period will be computed using EQ-5D-5L and SF-6D from the multiple imputed dataset. Cost-effectiveness analysis will be conducted by calculating the ICER between the two groups. Missing data in the costs will be imputed by intra-group mean values.

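### The listed imputation predictors omit intervention group, which shrinks the between-arm difference by about 5–20% if 20% of week-8 values are missing

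*Protocol article*

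**What the plan says.** The Statistical analysis section sets the method ("Multiple imputation will be used to fill the missing data"), fixes five imputed datasets and names the predictors: values are "imputed by the observation value of age, gender, body mass index, KL grade and outcomes from other timepoints". Intervention group does not appear, and imputation by arm is not mentioned.

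The same section defines the analysis set: "All randomly grouped patients with at least 1 session of intervention received will be included in the modified intention-to-treat (mITT) analysis". It then fits mixed-effect models to the repeated outcomes with "intervention as the main factor, and the baseline value as the covariate". Sensitivity analyses cover NRS and KOOS ADL only. One of them drops the imputation: "First, the dataset without imputation will be analyzed to address potential imputation bias".

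Two statements under Health economic evaluation bear on the point. Utilities come from the same imputation: "QALYs for each patient over the study period will be computed using EQ-5D-5L and SF-6D from the multiple imputed dataset". Costs are handled differently: "Missing data in the costs will be imputed by intra-group mean values". So imputation by group is stated for costs and not for outcomes.

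The Sample size section gives the only figure for expected loss: "Taking into account a 20% dropout rate".

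**The concern.** An imputation model should contain every variable whose coefficient the analysis model estimates. If arm is left out, two patients with the same covariates and the same observed scores get the same expected imputed value, whichever treatment they had. Their observed post-baseline scores carry part of the arm effect into the imputed value, but not all of it. Mixing these values with the observed ones shrinks the estimated difference.

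The trial sets out to find differences between two active treatments, so a shift toward zero favours a false reading of no difference. It reaches both primary outcomes. It also reaches the imputed secondary outcomes and the QALYs, for which no unimputed check is planned. The QALY difference is the denominator of the ICER. If it were 20% too small and the cost difference were unchanged, the ratio would be 1/0.8 = 1.25 times its proper value.

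**Working it through.** **Plan's own figure.** From Sample size: differences 1 (NRS) and 8 (KOOS), SDs 2 and 16, two-sided α 0.025, power 80%.

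- Per arm, n = 2(z₀.₉₈₇₅ + z₀.₈)²(SD/difference)² = 2 × (2.241 + 0.842)² × 4 ≈ 76.0, so 77. KOOS has the same ratio and also gives 77.
- The exact t-test gives 77.3, so 78. Then 78/0.8 = 97.5, so 98 per arm and 196 in total.

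The sample size reproduces and is not in dispute.

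**Simple bound.** Let p be the share of week-8 values missing, Δ the true difference, and k the share of Δ that imputed values retain:

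expected estimate = (1 − p)Δ + p·k·Δ

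Dropouts with no post-baseline score have k = 0, because none of the listed predictors then carries information on arm. With p = 0.20 the estimate is 0.8 × 1 = 0.8 NRS points, or 0.8 × 8 = 6.4 on KOOS ADL.

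**Simulation for the intermediate cases.** Taken from the article: N = 196, 1:1 allocation, SD 2, week-8 difference 1, five imputations, α 0.025, visits at baseline and weeks 4, 8, 16 and 24. Assumed, because the article does not give them:

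- 20% of patients affected, completely at random;
- equal between-visit correlation of 0.3, 0.5 or 0.7;
- an arm effect of 0.7 at week 4 and 1 at weeks 16 and 24;
- week-8 ANCOVA standing in for the mixed model.

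Imputation used chained Bayesian regression, pooled by Rubin's rules, with 300 trials per scenario. The simulation error of a power near 80% is therefore about √(0.8 × 0.2/300) = 2.3 percentage points.

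| Scores available for affected patients | Correlation | Mean estimate, printed list | Mean estimate, arm added | Power, printed list | Power, arm added |
|---|---|---|---|---|---|
| Baseline only | 0.3 | 0.782 | 0.974 | 60% | 75% |
| | 0.5 | 0.803 | 0.999 | 76% | 88% |
| | 0.7 | 0.795 | 0.990 | 92% | 95% |
| Half baseline only, half also week 4 | 0.3 | 0.824 | 1.009 | 68% | 79% |
| | 0.5 | 0.845 | 1.027 | 83% | 94% |
| | 0.7 | 0.826 | 0.993 | 93% | 97% |
| Baseline and week 4 | 0.3 | 0.844 | 1.010 | 70% | 79% |
| | 0.5 | 0.846 | 0.996 | 77% | 86% |
| | 0.7 | 0.855 | 0.989 | 94% | 97% |
| All except week 8 | 0.3 | 0.885 | 0.990 | 77% | 82% |
| | 0.5 | 0.918 | 1.002 | 91% | 92% |
| | 0.7 | 0.947 | 1.015 | 99% | 98% |

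Solving the formula above, k = (estimate − 0.8)/0.2. This gives about 0 for baseline-only dropout, about 10–30% where week 4 is available for some or all, and about 40–75% where only week 8 is missing. The same ANCOVA on unimputed data averaged 0.98 to 1.03, so the shrinkage comes from the imputation and not from the missingness.

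**Cross-checks.** A run of 3,000 trials per scenario at correlation 0.5 gave 0.80 (baseline only), 0.84–0.85 (with week 4) and 0.89–0.91 (only week 8 missing). A further run over correlations 0.3–0.7 gave 0.80–0.82, 0.85–0.88 and 0.90–0.93.

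**Share of the 20% inside the mITT set.** Patients lost before their first session are not imputed. Suppose half of the 20% never start. Then mITT missingness is 10/90 = 11%, and the worst-case estimate is about 0.89.

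**The case against.** **The list may not be complete.** The article condenses a fuller protocol, a SAP may exist, and the text does not say that arm is excluded. What can be asserted is that arm is not listed. Against that, the article gives a specific list of predictors and does state group-wise imputation for costs. A SAP that copied the list would inherit the fault. If the full documents already include arm, only the article's wording needs correcting.

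**A check is planned.** The unimputed analysis is meant to detect imputation bias and, for NRS and KOOS ADL, it would. This stands as a safeguard. However, the shrunken estimate remains the primary one, and the secondary outcomes and QALYs have no such check.

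**The loss may be well under 20%.** This stands. The 20% is a recruitment allowance, and the mITT rule removes anyone who never starts treatment.

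**Power may hold.** In part this stands. With week 4 available and correlation 0.5, the 3,000-trial run put power under the printed list at 80–82%, and at correlation 0.7 it exceeded 90% throughout. At correlation 0.3 with baseline-only dropout, power is 75% even with arm added. So not all of the gap between 60% and 80% is due to the omission.

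**Stronger readings to avoid.** A reader might infer that imputed values carry little or no arm effect. That fits only dropouts without post-baseline scores, because outcomes at other visits are among the predictors. A reader might also think five imputations too few. At a missing-information fraction of 0.2, relative efficiency is 1/(1 + 0.2/5) = 96%, and no harm has been shown. Nor has any bias been shown from leaving out hospital, sessions attended or rescue use. Shrinkage toward zero does not create false positives.

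**Conclusion.** The point holds as a fault in what the article states. Imputing from the printed list and then estimating the intervention effect biases that effect toward zero. The direction does not depend on the simulation settings, but the size does.

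At 20% missing, the shrinkage ranges from about 5% (only week 8 missing, high correlation) to about 20% (no post-baseline scores). On the planning effects, the worst case is 0.8 instead of 1 on NRS and 6.4 instead of 8 on KOOS ADL. Power can drop below 80% when dropouts have little or no post-baseline data or when correlation is low. In the simulation, the worst case is 60% against 75% with arm included.

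These figures rest on missingness completely at random, assumed correlations of 0.3–0.7, an assumed course of the arm effect, and ANCOVA in place of the mixed model. They are upper values if some losses fall outside the mITT set.

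**What to change.** State that intervention group is a predictor in the imputation model, or that imputation is run separately within each arm, and keep the predictors already listed. Apply the same rule to the EQ-5D-5L and SF-6D utilities from which QALYs are computed. In the simulation, adding arm brought the mean estimate back to 0.97–1.03 in every scenario.

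The cost is one sentence in the SAP or analysis specification and one more variable in the imputation step, settled before the outcome data are analysed. No new data or patients are needed. A coded arm label is enough, so the analysts can stay blinded. More imputations and further predictors are optional.

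### Read literally, the mixed model uses the baseline score both as a response and as the covariate; the sentence should say post-baseline scores and name the week-8 contrast

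*Protocol article*

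**What the plan says.** All sections cited are in the protocol article.

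- **Statistical analysis.** Every repeated continuous outcome, including both primary outcomes, is to be compared in a mixed model, which the section describes thus: "using outcome scores at all assessed timepoints as the dependent variable, intervention as the main factor, and the baseline value as the covariate". Nothing limits the response to follow-up visits.
- **Secondary outcomes.** For most of the other outcomes under that sentence: "Other secondary outcomes will be assessed at baseline and at week 4, 8, 16 and 24". For the two primary measures: "Additionally, the NRS and the KOOS ADL will be assessed at week 4, 16 and 24 as secondary outcomes".
- **Primary outcomes.** Both are changes "from baseline at week 8". The Allocation section has the remaining baseline measurements taken after the one-week preparation period and before the envelope is opened.
- **Sample size and significance level.** Differences are "expected to be 1 and 8 at week 8, respectively, with the standard deviations (SD) of 2 and 16". The design statement is "With 2-side α = 0.025 (adjusted for two primary outcomes), 77 patients per treatment group are required", and in the analysis P < "0.025 will be considered statistically significant (Bonferroni correction") applies to each primary outcome.

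**The concern.** By the article's own usage, baseline is a time at which outcomes are assessed. A response made up of the scores at every assessed time then gives each patient five rows, one of which is the covariate itself. In that row the covariate predicts the response perfectly, with slope 1, no residual error and no arm difference once the covariate is in the model. It carries no information about treatment, yet it enters the estimation.

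The damage depends on how the rest of the model is built. With intervention alone, the empty row is averaged into the treatment effect. With a separate effect at each visit, the week-8 estimate is protected, but the row pulls down the pooled residual variance and distorts the common baseline slope. Adding visit terms therefore does not by itself remove the problem. The sentence governs both primary tests, and no other model is named for the two sensitivity analyses, so those would not reveal the fault.

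**Working it through.** **Inputs from the article.** Difference 1 with SD 2 (NRS) and 8 with SD 16 (KOOS), standardised 0.5; two-sided 0.025 per primary outcome; 80% power; 77 per group; 196 in total after 20% dropout; visits at baseline and weeks 4, 8, 16 and 24.

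**Inputs assumed.** The article gives no correlations between visits and no covariance structure. Baseline-to-follow-up correlation was taken as 0.3 to 0.5 and follow-up-to-follow-up as 0.5 to 0.7, plus one AR(1) case with 0.7.

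**1. The plan's own figure.** n = 2(z₀.₉₈₇₅ + z₀.₈₀)² / 0.5² = 2(2.241 + 0.842)² / 0.25 ≈ 76.04, so 77 per group, as stated. The t-test version gives 78; 78 / 0.8 = 97.5, so 98 per group and 196 in total. The sample size is not in question.

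**2. Intervention as the only factor, baseline row kept.** With complete or fully imputed data, a random-intercept model estimates the arm effect from each patient's mean. Write Y₀ for baseline and F for the mean of the four follow-up scores. The five-row mean is (Y₀ + 4F)/5. The baseline covariate absorbs Y₀/5 exactly, so:

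- estimate = 4/5 × the baseline-adjusted difference in F;
- standard error = 4/5 × its standard error;
- the test statistic is unchanged.

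Simulation with 77 per arm agrees. For a true constant effect of 1, the estimate is 0.80 to 0.82 with the row and 1.00 to 1.02 without it. With correlations 0.3 and 0.6 the standard errors are about 0.201 and 0.252, and rejection rates are identical (0.0265 under no effect, 0.961 under the effect).

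- *Constant effect over weeks 4 to 24:* 1 × 4/5 = 0.8 and 8 × 4/5 = 6.4.
- *Assumed effect peaking at week 8 (0.5, 1, 0.5, 0.25):* the post-baseline average is 2.25/4 = 0.56, and 4/5 of that is 0.45. The simulated ranges are 0.55 to 0.57 and 0.44 to 0.46. Most of the distance from the week-8 value of 1 then comes from averaging over visits.
- *Interval coverage:* for estimate 0.80, standard error 0.201 and true average effect 1, the bias is 0.20/0.201 ≈ 0.995 standard errors. A nominal 95% interval covers Φ(1.96 − 0.995) − Φ(−1.96 − 0.995) ≈ 0.83. A nominal 97.5% interval covers Φ(2.241 − 0.995) − Φ(−2.241 − 0.995) ≈ 0.89.

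**3. Visit and intervention-by-visit terms with a random intercept (not stated in the article), week-8 contrast.** Simulated under no effect: 77 per arm, 4000 trials per setting, two-sided 0.025. The Monte Carlo standard error is √(0.025 × 0.975 / 4000) ≈ 0.0025.

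| Assumed correlations (baseline–follow-up / follow-up–follow-up) | Model SE / empirical SE, with row | Rejection, with row | Rejection, without row |
|---|---|---|---|
| 0.3 / 0.6 | 0.289 / 0.312 | 0.0413 | 0.0278 |
| 0.5 / 0.5 | 0.258 / 0.282 | 0.0405 | 0.0285 |
| 0.5 / 0.7 | 0.258 / 0.288 | 0.0442 | 0.0283 |
| 0.4 / 0.7 | 0.276 / 0.297 | 0.0415 | 0.0255 |
| AR(1), 0.7 | 0.268 / 0.276 | 0.0305 | 0.0210 |

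The standard error is understated by 1 − 0.268/0.276 ≈ 3% to 1 − 0.258/0.288 ≈ 10%. The week-8 estimate itself is unbiased (0.99 to 1.03 for a true 1). A second set with 98 per arm, exchangeable correlation 0.3 to 0.7 and baseline SD 1.5 to 2 gave 0.035 to 0.045 with the row and 0.020 to 0.027 without it. If the test were instead taken on the interaction coefficient relative to baseline, the rate with the row ranged from 0.024 (all correlations 0.5) to 0.060, so the size depends strongly on the assumptions.

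**The case against.** The strongest reply is that the sentence has a conventional, harmless reading. It names baseline separately as the covariate, and most statisticians would take that to mean follow-up scores adjusted for baseline. For NRS and KOOS ADL the article uses the word assessed only of follow-up visits ("Additionally, the NRS and the KOOS ADL will be assessed at week 4, 16 and 24 as secondary outcomes"); the sentence that lists baseline concerns other outcomes. On that reading neither harm occurs.

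This stands as far as intent goes: a reader might infer that the trial will certainly fit baseline on both sides, and the article does not show that. It does not rescue the wording. The sentence on NRS and KOOS ADL also leaves out week 8, the primary time, so it cannot be the full list of their assessed visits. The same model sentence also covers outcomes for which baseline is expressly an assessed time.

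Three further objections stand and limit the point:

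- In the form with intervention alone, the test is untouched. A reader might infer lost power or a wrong error rate there; the test statistic is the same with and without the row.
- The planned differences are given for week 8 only, while treatment ends at week 8 and follow-up runs to week 24. That 1 and 8 would be reported as 0.8 and 6.4 does not follow without a constant effect.
- The raised error rate belongs to a model that the article does not state. A condensed article may leave visit terms and covariance to a fuller document, so their absence is not the complaint. The two harms are alternatives and cannot both apply to one fitted model.

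**Conclusion.** Wrong as written, on its literal wording: the baseline score is both a response row and the covariate. The consequences are conditional.

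- **Intervention as the only factor:** the estimate and standard error are each 4/5 of what they should be for the average post-baseline effect. The effect is biased and its interval too narrow; the P < 0.025 decision is the same. This rests on complete or fully imputed data.
- **Week-8 contrast from visit and intervention-by-visit terms with a random intercept:** the standard error is generally too small, and a nominal 0.025 test runs at roughly 0.03 to 0.045. This rests on an unstated model and assumed correlations, and the inflation is small under AR(1).
- **Only follow-up scores meant:** neither applies.

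The documents do not support the stronger claim that the primary analysis is invalid or that the trial is underpowered. What they support is that the sentence fixing both primary tests admits a faulty model and should be closed to it.

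**What to change.** Reword the model sentence in the Statistical analysis section so that:

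- the response is the score at the post-baseline visits only (weeks 4, 8, 16 and 24);
- the model contains intervention, visit and intervention-by-visit, with the baseline value as covariate;
- the primary test is the week-8 between-group contrast.

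The last two items are needed because dropping the baseline row alone would still leave an average over weeks 4 to 24, not the week-8 endpoint.

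An equally sound alternative is to keep baseline in the response, drop it as covariate, constrain the arm means to be equal at baseline, and again test the week-8 contrast. The two approaches should not be combined.

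The cost is one sentence. No data, patients or change in sample size are needed, and the Study status section reports recruitment as still under way, so the wording can be settled before analysis.
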